#### Measures

Based on treatment episode and client admission information in the CDS and claims information in Medicaid, clinic level covariates, quality, and outcomes data will be computed in 6-month assessment windows. Client level covariates from the CDS will include frequency of use, injection drug use, age, gender, race/ethnicity, education, residential stability/homelessness, and psychiatric comorbidities at admission. Medicaid claims will be used to identify OUD medications, various health conditions based on ICD-10 diagnosis fields; healthcare episodes based on procedure, rate and NDC codes; and cost based on Medicaid payments for claims and encounters. Clinic rates of 6-month retention will be computed from admission and discharge dates in the CDS. OUD medication initiation and adherence will use data from Medicaid pharmacy claims during an episode. Initiation will be a new OUD medication pharmacy claim within 30 days and adherence will be computed using the NQF 3175 definition [51–53]. Overdoses will be identified by CDC defined combinations of diagnoses and acute care procedure codes [54, 55]. All-cause ED visits will be defined by procedure and rate codes. HCV infections will be defined by diagnoses during any hospitalizations or on two outpatient claims [56, 57]. Costs of healthcare services will be drawn from Medicaid claims and encounter data.

Provider-level covariates will also be calculated. SUD program characteristics will be drawn from computing provider-level statistics from claims as well as from state databases that contain addresses, affiliations, and licensing information. Provider variables will include geographical location, annual census, and hospital affiliation. Geographical information of provider location will be drawn from the Area Health Resources File: poverty, population density, ethnic/racial population, and health professional availability.

Client-reported treatment process improvement will be computed from change scores on the eTPA8 from baseline to latest administration. Further, the client-self reported mobile survey will include the following measures: (1) past 2-week use of opioids and other substances based on the Addiction Severity Index (ASI) [58], (2) substance use consequences based on the Short Inventory of Problems-Revised (SIP-R) [59], (3) health-related quality of life based on the first item of the SF-36 [60], (4) functional outcomes using the Treatment Effectiveness Assessment [61], past 30-day employment, incarceration, housing status based on the ASI, (5) a visual analog scale measuring cravings to use substances [62], and (6) demographics.

Staff surveys will include measures on practice change capacity (i.e., the change process capability questionnaire) [63, 64], the Opinions About MAT Survey [65], knowledge and perceptions about person-centered care and shared-decision making, and use of data and quality metrics. An interview guide for staff qualitative interviews will be created to reflect the dimensions of the i-PARIHS model (e.g., inner context) [66].

The marginal cost of the CARE intervention will be estimated to inform future intervention development and implementation. We will collect detailed data on staffing and other resources to inform micro-costing computations and estimates of the marginal costs of deploying CARE under real-world conditions [67–69]. Cost data collection will follow generally accepted practice in cost-effectiveness research [67, 68]. In addition, the cost collection procedures and estimations will borrow from methods derived from process engineering [70] and managerial accounting [71–74]. Input prices (i.e., cost of each unit of resource input) will be derived from market rates when available, program budgets, or government pricing schedules (e.g., Bureau of Labor Statistics data on personnel costs for the Northeast region). The first step in the cost tracking will entail developing detailed process maps in conjunction with intervention developers and clinicians to identify all key processes [75]. The cost tracking system will track resources used to deliver the intervention as well as identify research protocol driven costs that would not be part of a real-world implementation [76]. The cost tracking system will identify intervention development costs as well as operational costs associated with running the intervention.

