Hypothesis 2: Positive change in the eTPA8 scale will be associated with longer retention and reduced substance use at follow-up.Aim 3: Examine whether there are program admission changes in terms of client complexity (e.g., homelessness, psychiatric conditions) to test impact on client access (i.e., adverse selection) as clinics monitor quality measures.
Hypothesis 3: Clinic rates of severe OUD (i.e., daily use and/or injection use), homelessness and psychiatric conditions at admission during the year following the CARE intervention will decrease from baseline rates.Aim 4: Examine staff attitudes, experiences, and behaviors related to (1) implementing the eTPA8 and clinical practice change, and (2) working with external facilitators to implement QI processes.Aim 5: Estimate addiction program and state intervention costs of CARE and impact on Medicaid costs.

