### Measures and materials

#### Data sources

The NYS OASAS registry of all admissions and discharges (irrespective of payer) to licensed addiction treatment facilities—the Client Data System (CDS)—forms the basis of our administrative data set. The CDS will record all treatment episodes that occur in the 30 clinics we include in this study, providing a rich source of data. All licensed providers of SUD treatment in NYS are mandated to submit admission and discharge data into the CDS. NYS OASAS tracks each individual by unique identifiers. When clients enter treatment, providers enter information on demographics, level of functioning (e.g., health status, comorbidities), criminal justice status, recent history and frequency of substance use, and recent SUD treatment history. Upon discharge, providers enter information on functional status (e.g., employment, housing), source of payment for treatment (e.g., self-pay, Medicaid, private insurance), criminal justice involvement during treatment, hospitalizations, and use of ED services. Additionally, the discharge information has type, frequency (i.e., number of sessions), and intensity of SUD treatment as well as discharge status (discharge disposition and goal achievement). NYS Medicaid claims will supplement the administrative dataset by providing data on OUD medications and health services use (e.g., ED visits). We will link clients in Medicaid to the CDS using the NYS OASAS identifier augmented, in cases where there were no exact matches, by searching for same treatment events that were recorded in each database. Additionally, we will employ probabilistic matching techniques to account for data entry errors on elements of the OASAS identifier. Our link rate in previous studies among OUD individuals in Medicaid is 90% [47].

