### Analysis and power

The primary aim of this study is to test whether CARE is associated with greater use of pharmacotherapy for OUD, longer retention in care, and improved recovery outcomes (e.g., reduced drug use). We will employ multiple convergent analytical methods to (a) examine CARE implementation and (b) test association between CARE and OUD treatment outcomes. Analyses will begin with examination of distributions of variables and transformations where appropriate, examination of patterns of missingness, and application of formal imputation methods [77–79] if deemed essential to project aims. Analyses for Aims 1, 2, and 3 will utilize general linear mixed models (GLMM) for stepped-wedge designs [80–85]. For example, to test the effect of CARE on treatment process quality measures (i.e., initiation and adherence to OUD medications, in-treatment symptom and therapeutic progress, 6-month treatment retention) and recovery outcomes (substance use, overdoses, self-reported health status, HCV infection, and ED visits), we will employ stacked difference-in-difference models that test for within and across clinic changes while adjusting for secular trends across time [80, 86, 87]. The models will take the form: *Y*_*ikt*_ = *μ* + *X*_*kt*_*θ* + *β*_*t*_ + *Z*_*ikt*_ + *α*_*k*_ + *e*_*ikt*_, where *β*_*t*_ is a fixed effect for time, *Z*_*ijk*_ is a matrix of covariates measuring individual, geographical, and clinic characteristics for person *i* in clinic *k* at time *t, X*_*kt*_ is an indicator for intervention in clinic *k* at time *t* (coded 0 for baseline then 1 from when intervention begins in clinic through end of study), and *θ* is the treatment effect. *Y*_ikt_ represents a matrix of binary variables: treatment process quality measures (i.e., pharmacotherapy initiation and adherence, in-treatment symptom and therapeutic progress, treatment retention) and recovery outcomes (i.e., substance use, overdoses, self-reported status, HCV infection, and ED visits). We will estimate the effect of CARE (*θ*) while controlling for secular trends (*β*) and adjusting for clustering within clinic (*α*_*k*_) using robust standard errors. We will also conduct a set of falsification tests. These will include (1) testing for variation in program and client characteristics across time of enrollment; (2) examination of variation across study time in the study outcomes for clinics not participating in the study; and (3) examination of variation in intervention effect based on clinics’ baseline levels of quality measures (e.g., comparing top third to bottom third in quality of care at baseline).

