
To examine Aim 4, we will use a concurrent triangulation mixed-methods design such that staff quantitative and qualitative data collection will occur concurrently and results will be integrated after analysis of each [88]. The semi-structured interviews will be transcribed and analyzed using conventional qualitative content analysis [89] following the process outlined in Erlingsson and Brysiewicz [90]. Atlas.ti will be used to manage the data. A codebook will initially be created based on i-PARIHS constructs and will be modified and amended as coding and analysis continues. For the quantitative results, multilevel modeling will be used to examine change over time in survey scores given the nested structure of the data (staff nested within clinics) [91].

For Aim 5, the cost analysis will focus on the provider and state agency perspective as the main decision-maker; consequently, other societal costs are not included in this preliminary analysis. Decision analytical models will be created using measures of central tendency (e.g., means, medians) of observed resource inputs as well as measured estimates of variances for sensitivity analyses. Using TreeAge Pro [92], we will estimate average costs as well as confidence intervals based on simulations drawing from variances of model inputs. We will conduct a series of one-way and two-way sensitivity analyses across model inputs to determine the impact of variability of individual model parameters. Additionally, we will use Monte Carlo simulation to build confidence intervals over which the cost of the intervention may vary. Costs will be presented as ratios: per clinic, per participant, and per unit of each quality measure.

We will also examine the association between CARE and total Medicaid costs. Costs will be modeled using generalized gamma models (GGM), which offer flexibility in modeling non-Gaussian outcomes by computing three parameters to fit the observed distribution: location, scale, and shape [93, 94]. One advantage of GGM is that it is not subject to the retransformation bias stemming from heteroscedasticity in the log-scale often associated with the more common OLS regression on log-transformed healthcare costs [94–96]. We will consider other GLM approaches to analyzing costs and subject these to goodness of fit tests as outlined by Manning [97].

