To estimate study power for select outcomes, we drew from methods developed by Hussey and Hughes [80] as implemented in a Stata command, stepped wedge [98]. Using administrative data to estimate sample sizes and baseline rates (μ), we computed detectable differences for a β = 0.80, α = 0.01, ICC/ρ = 0.20, and SW-RCT with 6 crossover points, and 5 clinics randomized at each point. For 6-month retention, assuming step samples sizes (*m*_k_) of 132 and base rate (μ) of 25%, we will be able to find a 2.8pp change in retention (i.e., 27.8%) to be statistically significant and clinically meaningful. We also conducted sensitivity analyses varying ρ (0.10–0.30) and β (0.90) and found detectable differences ranging from 2.6 to 3.2%. For OUD medication initiation, we assume *m*_k_ = 40 Medicaid clients with OUD, μ = 0.40, and find a detectable difference of 6.7%. For ED visits, we assume *m*_k_ = 79 Medicaid clients and μ = 0.40, and find a detectable difference of 3.9%. Consequently, with 30 clinics and 6 steps in our SW-RCT, we will have power to detect moderate and clinically meaningful differences in outcomes.

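### The plan names no pre-admission ED-visit, overdose or cost value as a covariate for the Medicaid-based outcomes; adding one is cheap and would mainly gain precision

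*Protocol article*

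**What the plan says.** In the protocol article, Measures, the client-level covariates are tied to the registry (CDS): "Client level covariates from the CDS will include frequency of use, injection drug use, age, gender, race/ethnicity, education, residential stability/homelessness, and psychiatric comorbidities". The same section gives Medicaid claims a different job: "Medicaid claims will be used to identify OUD medications, various health conditions based on ICD-10 diagnosis fields", together with healthcare episodes and cost. Overdoses and all-cause ED visits are defined there from claims-type codes. Data sources describes the person-level link between the two databases and says: "NYS Medicaid claims will supplement the administrative dataset by providing data on OUD medications and health services use (e.g., ED visits", with a 90% link rate in earlier work among people with OUD in Medicaid.

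In Analysis and power, the covariate term Z of the outcome model "is a matrix of covariates measuring individual, geographical, and clinic characteristics for person", indexed by client, clinic and window. No baseline value of an outcome is mentioned. For costs the section says: "We will also examine the association between CARE and total Medicaid costs". It then names generalized gamma models and gives no covariates.

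The ED power statement assumes 79 "Medicaid clients and μ = 0.40, and find a detectable difference of 3.9" percent. Hypothesis 3, in Background, predicts a fall against baseline in these rates: "Clinic rates of severe OUD (i.e., daily use and/or injection use), homelessness and psychiatric conditions at admission during the year following the CARE intervention will".

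**The concern.** Clinics are randomized to start dates; clients are not randomized. The clients admitted after a clinic starts CARE are, in the main, different people from those admitted before. The clinic effect in the model removes a clinic's constant level, but it does nothing about differences between clients within a clinic.

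A client's own earlier ED use, overdose or cost is a natural predictor of the later value, and leaving it out has two possible consequences:

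- **Precision.** Within-clinic residual variance drives the standard error of the CARE effect in this design. A covariate that explains some of that variance reduces the detectable difference.
- **Case mix.** If admissions after CARE differ in prior acute-care use beyond what the listed covariates capture, the estimated effect on ED visits, overdoses or costs would absorb that difference.

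The cost model is the most exposed of the three, because no adjustment of any kind is named for it.

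**Working it through.** **1. Are the Hypothesis 3 characteristics covered?** Each one set against the covariate list in Measures:

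| Hypothesis 3 | Listed covariate |
|---|---|
| Daily use | Frequency of use |
| Injection use | Injection drug use |
| Homelessness | Residential stability/homelessness |
| Psychiatric conditions | Psychiatric comorbidities |

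All four are listed. Prior ED use, overdose and cost are not.

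**2. Inputs for precision.** From Analysis and power: ICC 0.20, α = 0.01, power 0.80, 6 steps of 5 clinics; retention m = 132 and base rate 0.25; ED visits m = 79 and base rate 0.40. Assumed: two-sided test, 7 windows (one baseline plus six steps), m per clinic and window. Also assumed is r, the within-clinic correlation of the prior value with the outcome, given the other covariates. The documents give no value for r, so a range of 0.2 to 0.5 is shown.

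**3. Formula (Hussey and Hughes).** With I = 30 and T = 7, the design constants are U = 105, W = 2275 and V = 455. Then IU − W = 875 and U² + ITU − TW − IV = 11025 + 22050 − 15925 − 13650 = 3500, so

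Var(θ) = 30·s²·(s² + 7τ²) / (875·s² + 3500·τ²)

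where s² = 0.8·p(1−p)/m and τ² = 0.2·p(1−p). The detectable difference is (2.576 + 0.842) × SE.

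**4. Check on the plan's retention figure.** s² = 0.15/132 = 0.001136 and τ² = 0.0375. SE = 0.00824 and the detectable difference is 2.82 points, against 2.8 stated. The formula reproduces it.

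**5. ED visits without the prior value.** s² = 0.192/79 = 0.002430 and τ² = 0.048. SE = 0.01204 and the detectable difference is 4.12 points. The article states 3.9. That mismatch is a separate matter and plays no part here; the comparison below starts from 4.12.

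**6. ED visits with the prior value.** Replace s² by s²(1 − r²). Because τ² is large relative to s², Var(θ) is close to 0.06·s², so the detectable difference shrinks by about √(1 − r²).

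| Assumed r | Detectable difference | Reduction | Power at an effect that had 80% | If listed covariates already explain half of r² |
|---|---|---|---|---|
| 0.2 | 4.03 pp | 2% | 81.9% | 4.07 pp |
| 0.3 | 3.93 pp | 5% | 84.3% | 4.02 pp |
| 0.4 | 3.77 pp | 8% | 87.5% | 3.95 pp |
| 0.5 | 3.57 pp | 13% | 91.4% | 3.85 pp |

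**7. Case-mix bias, as a ceiling only.** Bias = change in the share of admissions with recent ED use × the difference in ED rate between those clients and the rest. Both factors are assumptions. A change of 2 to 10 points and a difference of 0.1 to 0.3 give 0.02 × 0.1 = 0.2 pp up to 0.10 × 0.3 = 3.0 pp. These figures suppose that the listed covariates explain none of the shift. Only the unexplained part would remain, and the documents do not allow that part to be sized.

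No figure can be worked out for overdoses or costs, because the article gives no base rate or variance for them.

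**The case against.** Three objections carry weight.

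**The text does not exclude the covariate.** A reader might infer that these analyses will not adjust for prior values. The documents do not support that. The sentence in Measures covers registry covariates only and is worded as an open list. Z is described generically, and silence about the cost model's covariates is not a statement that there are none. This is a condensed article, and neither the full protocol nor the SAP is shown. What stands is that the article does assign covariates to sources in some detail, and this one, available from a source already being linked, is not among them.

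**Hypothesis 3 does not supply the bias argument.** A reader might also infer that the ED, overdose and cost effects are left open to the very shift that Hypothesis 3 predicts. They are not, at least where the listed covariates enter the model, since every characteristic in that hypothesis is listed. The plan also includes a falsification test of client characteristics across time of enrollment, and Aim 3 studies the shift itself. Those checks could reveal a shift without correcting the estimate, but a remaining shift in prior acute-care use is a possibility and not something the plan forecasts.

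**The gain rests on an assumed correlation and on prior enrollment.** At r of 0.3 or below the gain is small. The claims hold a prior value only for clients enrolled in Medicaid before admission, which the article does not require or describe. Both points stand, and they limit the size of the concern.

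**Conclusion.** The point holds as a worthwhile, low-cost improvement and not as an error in the plan. The article names no pre-admission value for ED visits, overdoses or costs, although claims already being linked could supply one for clients with earlier coverage.

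The expected benefit is mainly precision: for ED visits, a detectable difference 2% to 13% smaller over the assumed range of r, and less where the listed covariates already share that information. The second benefit, protection against a residual shift in prior acute-care use, is real in principle but cannot be sized from the documents. It matters most for the cost model, for which no covariates are named.

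The figures rest on a two-sided test, seven windows, a constant clinic effect and the assumed r.

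**What to change.** Name the following in the main models before outcome data are analyzed:

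- **ED model:** add to Z whether the client had any ED visit in the look-back.
- **Overdose model:** add to Z whether the client had any overdose in the look-back.
- **Cost model:** include the client's total Medicaid cost in the look-back, together with the client-level covariates already listed in Measures.
- **Look-back:** use one fixed window, the 6 months before the client's first study admission, and carry that value to later episodes. The value then precedes any exposure of that client to CARE. For readmitted clients it may be old.
- **Incomplete coverage:** give clients without full Medicaid coverage in the window their own category, and add a sensitivity analysis restricted to fully covered clients. The category alone is weak protection when clients are not randomized.

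The cost is a few lines of analysis-plan wording and a 6-month look-back in claims that are already being linked. No new data collection and no change to the design are needed. The main downside is the handling of clients with incomplete earlier coverage, whose number the documents do not give.

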In this paper, we describe a study protocol for a stepped-wedge randomized controlled trial (SW-RCT) stemming from a state-academic partnership that will test a multicomponent, clinic-level intervention, called Coaching for Addiction Recovery Enhancement (CARE). We will test whether CARE improves treatment process quality and recovery outcomes over treatment as usual, particularly for OUD. The SW-RCT design was selected mainly because the intervention is conducted at the clinic-level and, from a resource perspective, it would be impractical to provide the intervention to all clinics at once given the facilitation model being utilized. Further, the stepped-wedge design was seen as more acceptable and ethical for key program stakeholders (notably the single state agency that regulates SUD treatment [SSA]) due to the potential benefits from the resources being provided as part of the intervention package (e.g., training support from the SSA) compared to a parallel randomization design. The CARE intervention includes the following components: (1) staff clinical training and tools, (2) quality improvement and change management training, (3) external facilitation to support implementation and sustainability of quality improvement, and (4) the eTPA8 client-reported treatment progress tool to support data-driven decision making and clinic-level quality measurement. See Fig. 1 for our intervention conceptual model. We describe intervention components in more detail in the method section. Study aims and hypotheses are the following:
Aim 1: Test the effect of CARE on treatment process quality measures and recovery outcomes.
Hypothesis 1: CARE will improve clinic-level rates of treatment process quality measures (i.e., initiation of and adherence to OUD medications, in-treatment symptom and therapeutic progress, 6-month treatment retention) and recovery outcomes (i.e., substance use, overdoses, self-reported health status, hepatitis C infection [HCV], and emergency department [ED] visits).Aim 2: Examine association of changes in the eTPA8 client-reported treatment progress tool with treatment retention and substance use outcomes.

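### The HCV outcome as defined counts diagnosed infection whether or not it predates admission, so a change in it would not by itself show that CARE changed HCV infection

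*Protocol article*

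**What the plan says.** All passages are in the protocol article.

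- **Definition (Measures):** "HCV infections will be defined by diagnoses during any hospitalizations or on two outpatient claims". Two sources are cited for it; they are not at hand.
- **Window (Measures):** "clinic level covariates, quality, and outcomes data will be computed in 6-month assessment windows".
- **Role (Background, Hypothesis 1):** CARE is expected to improve "recovery outcomes (i.e., substance use, overdoses, self-reported health status, hepatitis C infection [HCV], and emergency department [ED] visits".
- **Model (Analysis and power):** the binary responses include "recovery outcomes (i.e., substance use, overdoses, self-reported status, HCV infection, and ED visits". The model has fixed time effects, a clinic term, covariates and an additive treatment effect.
- **Client covariates (Measures):** "frequency of use, injection drug use, age, gender, race/ethnicity, education, residential stability/homelessness, and psychiatric comorbidities at admission". HCV status at admission is not listed.
- **Contrast (Measures):** for medication, newness is written into the rule: "Initiation will be a new OUD medication pharmacy claim within 30 days".

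**The concern.** HCV can be present long before a client enters treatment. Take a client infected years earlier and admitted after the clinic has crossed over. Two outpatient claims carrying an HCV code, or one hospital stay with that diagnosis, make the client an event under CARE. The same client with fewer coded encounters is not an event. The quantity measured is therefore diagnosed HCV in a window: infection from any time, multiplied by the chance that it is coded.

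CARE cannot alter infections acquired before admission. It may alter the chance of coding, because it aims to raise medication use and retention. It may also coincide with a change in who is admitted: Hypothesis 3 expects severe OUD, which includes injection use, to become less frequent at admission. At stake is whether an apparent HCV benefit or harm could be attributed to CARE.

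**Working it through.** **No HCV figure to reproduce.** The article states no HCV rate, effect or power. All HCV inputs below are assumptions.

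**Does anything else in the article separate prior from new infection?**
- Time effects remove trends common to all clinics. Clinic terms remove stable differences between clinics. Neither removes a change in coding or case mix that arrives with crossover.
- Injection use at admission is adjusted for, but it captures past exposure only in part.
- The falsification tests cover characteristics over enrolment time, outcomes in non-participating clinics, and effect by baseline quality. None splits HCV into prior and new.

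**Illustration.** Let π be the proportion infected at admission (assumed 0.10-0.40), ι the six-month incidence among the uninfected (0.01-0.04), and D the chance that an infection meets the claims rule (0.50, the same for old and new infections). CARE cuts new infection by 25%.

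- Measured proportion: D × [π + (1−π)ι]
- Share predating admission: π / [π + (1−π)ι]
- Change with D stable: −D × (1−π) × ι × 0.25
- Relative rise in D that cancels the benefit: [π + (1−π)ι] / [π + 0.75(1−π)ι] − 1
- Change if D goes from 0.50 to 0.55: 0.55 × [π + 0.75(1−π)ι] − 0.50 × [π + (1−π)ι]

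| π | ι | Share predating | Change, D stable (pp) | Cancelling rise in D | Change, D 0.50→0.55 (pp) |
|---|---|---|---|---|---|
| 0.10 | 0.01 | 91.7% | −0.11 | 2.1% | +0.42 |
| 0.10 | 0.04 | 73.5% | −0.45 | 7.1% | +0.19 |
| 0.40 | 0.01 | 98.5% | −0.08 | 0.4% | +1.95 |
| 0.40 | 0.04 | 94.3% | −0.30 | 1.4% | +1.79 |

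**Sensitivity to the detection assumption.** Suppose every new infection is detected and only old ones move from 50% to 55%. The change is then 0.05π − 0.25(1−π)ι: +0.28, −0.40, +1.85 and +1.40 pp in the same order. The sign does not reverse at 10% prevalence and 4% incidence.

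**The other direction.** With D = 0.50 unchanged and no effect on new infection, a one-point fall in π lowers the measure by 0.50 × 0.01 × (1−ι) = 0.48 to 0.50 pp. That exceeds the largest true benefit in the table (0.45 pp).

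**A different detection model agrees.** Take P(coded) = 1 − (1−h)e^(−L)(1+L), with a 5% chance of a hospital code (h) and a mean of 0.5-1.0 HCV-coded outpatient claims per window (L). With prevalence 10-50%, incidence 1-3% and a 30% cut in new infection, the measure moves by −0.02 to −0.24 pp if contact is stable, and by +0.07 to +1.7 pp with 10% more coded contact.

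**Precision.** The Hussey-Hughes variance with 30 clinics, 7 periods, ICC 0.20, two-sided α 0.01 and power 0.80 gives 2.82 pp for retention (m = 132 per clinic-period, base rate 25%), against the stated 2.8 pp. It gives 4.1 against the stated 3.9 for ED visits and 5.8 against 6.7 for medication initiation, so I use it for order of magnitude only. With the 79 Medicaid clients assumed for ED visits, and D = 0.50:
- Outcome as defined (measured base rate 5.5-21%): detectable difference 1.9-3.4 pp, against a true effect of 0.08-0.45 pp.
- New infections only, among the 79(1−π) uninfected (base rate 0.5-2%): detectable difference 0.6-1.5 pp, against 0.50 × 0.25 × ι = 0.125-0.50 pp.

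Corner by corner, the true effect is 2-21% of the detectable difference as defined and 16-40% after restriction. Restriction helps but does not make the outcome well powered.

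**The case against.** **The article is condensed.** A full protocol exists, and it or the cited sources may contain a look-back. That is fair, and the point concerns only the rule the article fixes. But the article chose to state the rule, and applying it as written counts old infections. The contrast with medication initiation carries little weight, since initiation implies a new claim anyway.

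**Prevalent cases cancel.** The model estimates an additive effect with clinic and time terms. If ascertainment and case mix are stable, prior infections drop out of the absolute difference and the effect on new infection remains, with more noise. This stands. A reader might infer that the outcome can never show an effect of CARE on HCV; the documents do not support that.

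**The direction is unknown.** A reader might also infer that the definition must work against CARE because retention brings more coded visits. Nothing in the article says that retention in an addiction clinic generates HCV-coded claims. One limb of the rule is hospitalization, and Hypothesis 1 expects fewer overdoses and ED visits, which could mean fewer hospital codes. The case-mix shift in Hypothesis 3 would likewise favour CARE. This stands too.

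**The sizes are assumed.** They are, and sign reversal is not universal, as the unequal-detection case shows.

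**The reach is limited.** HCV is one of several Hypothesis 1 outcomes and has no power calculation. Retention and medication results are untouched.

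**Conclusion.** The concern holds in limited form. As the article defines it, the HCV outcome is diagnosed HCV in a window, not new infection, and no listed covariate, model term or check separates the two. Under the assumed ranges, 74-98% of infections would predate admission. Small shifts in detection (0.4-7.1% relative) or in prevalence at admission (one point) are as large as the whole benefit of a 25% cut in new infection. An observed rise or fall would therefore not by itself show that CARE changed HCV infection. With stable detection and case mix the cost is precision, not a wrong sign. The direction of any bias is not established, and every size is illustrative because the article gives no HCV rates. The definition should be changed; the trial's other outcomes do not depend on it.

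**What to change.** 1. Define the outcome as the first qualifying HCV diagnosis after admission, among Medicaid clients with no HCV diagnosis in a fixed claims look-back before admission (for example 12 months).
2. Use prior HCV as a baseline covariate or as a case-mix descriptor under Aim 3.
3. State the residual bias. A look-back removes known prior diagnoses, but old undiagnosed infections first coded after more contact still count as new.
4. If incident cases are expected to be too few, which the precision check makes plausible, report HCV descriptively and do not test it as an outcome that CARE improves.

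**Cost:** a change of definition and a query in Medicaid claims the trial already plans to obtain. There will be fewer events, and clients without look-back enrolment drop out of this one outcome.
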